### Ethics and trial registration

CRC patients who meet the inclusion criteria will be completely informed about the protocol of the study. The protocol of this study was approved by the Medical Ethics Committee of Ahvaz Jundishapur University of Medical Sciences and is in conformity with the Declaration of Helsinki (approval number IR.AJUMS.REC.1396.1077). Each participant will sign the informed consent form. This clinical trial was registered on Iranian Registry of Clinical Trials (IRCT registration number IRCT20180306038979N1; http://irct.ir/user/trial/20288/view).

### Sample size

The number of participants was calculated according to the alterations in TNF-α between the control and co-supplementation groups and based on the study conducted by Mohammadzadeh et al. [25]. It was calculated with the use of fixed factor levels model (determining sample size for analysis of variance) [26] and considering sigma (standard deviation of TNF-α) of 1.25, 90% power, α of 0.05, resulting in 20 patients for each group. To allow for attrition, 25 patients will be recruited for each group. Collectively, a sample of 100 patients with stage II or III CRC will be enrolled.

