### Statistical analysis

All analyses will be performed with STATA statistics software, version 11.0 (STATA Corporation, College Station, EUA). Kolmogorov-Smirnov test will be used to assess normality of data. Quantitative and normally distributed parameters will be expressed as mean + standard deviation. Quantitative and non-normally distributed data will be shown as median and interquartiles. Analysis of variance (ANOVA) test will be used for comparing the values between and within groups. Analysis of covariance (ANCOVA) will be used to identify any differences between the four groups at the end of study, adjusting for baseline values and covariates (such as dietary intake, physical activity, and sun exposure). Bonferroni will be used to pairwise comparisons for the values after the intervention.

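### The 90% power can hold for the four-group test but is not shown for the Bonferroni-adjusted pair that answers the co-supplementation question

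*Protocol article*

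**What the plan says.** Protocol article, Sample size: "The number of participants was calculated according to the alterations in TNF-α between the control and co-supplementation groups". The method is named: "It was calculated with the use of fixed factor levels model (determining sample size for analysis of variance". The inputs and result are "considering sigma (standard deviation of TNF-α) of 1.25, 90% power, α of 0.05, resulting in 20 patients for each group", raised to 25 per group for attrition. The section gives no TNF-α difference and mentions no adjustment for multiple comparisons.

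Protocol article, Randomization and blinding: there are four groups (both supplements, vitamin D only, omega-3 only, double placebo).

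Protocol article, Statistical analysis: "Analysis of covariance (ANCOVA) will be used to identify any differences between the four groups at the end of study", adjusted for baseline and covariates. Then: "Bonferroni will be used to pairwise comparisons for the values after the intervention". The number of pairs is not given, and no pair is singled out.

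**The concern.** The trial takes its size from one contrast, control versus co-supplementation. A four-group test does not isolate it, because a significant result could come from vitamin D alone or omega-3 alone. Among the tests named in the analysis section, only the pairwise comparison speaks to co-supplementation against placebo, and that comparison is made at a stricter level than the 0.05 in the sample-size calculation. Someone who takes the 90% as the chance of showing a co-supplementation effect on TNF-α may be relying on a figure that belongs to a different test. The contrast that sets the sample size also bears the multiplicity cost of five comparisons that did not.

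**Working it through.** **Inputs from the Protocol article.** SD 1.25, α 0.05, power 90%, n = 20 per group, four groups (Sample size; Randomization and blinding); Bonferroni for pairs (Statistical analysis).

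**Inferred or assumed.** Four groups give 4 × 3 / 2 = 6 pairs, so the pairwise level is 0.05/6 = 0.00833. The target difference d (in SD units) is not stated, so 20 per group cannot be reproduced from the stated inputs alone. I solved instead for the differences at which 20 is the smallest n giving 90% power at α 0.05, under three readings.

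**Step 1: differences consistent with n = 20.** For the four-group F test (df 3 and 76), the noncentrality is λ = n Σ(μᵢ − μ̄)²/σ², and 90% power needs λ = 14.92.
- Reading A, F test with the other two means midway: λ = 20 × d²/2 = 10d², so d = √1.492 = 1.22. Because n = 19 is enough from about 1.255, the range is 1.22-1.25. Check at d = 1.25: F-test power is 0.897 at n = 19 and 0.914 at n = 20.
- Reading B, two-group t test (df 38), two-sided 0.05: d = 1.05-1.08.
- Reading C, F test with only co-supplementation differing: λ = 20 × 0.75d² = 15d², so d = √0.995 = 1.00; range 1.00-1.02.

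**Step 2: power of the pair.** Two-sided t test with pooled df 4 × 20 − 4 = 76 and noncentrality d√(n/2) = d√10. Critical values are 2.709 at 0.05/6 and 1.992 at 0.05.

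| Reading | d (SD) | Difference at SD 1.25 | d√10 | Power at 0.0083 | Power at 0.05 | n per group for 90% at 0.0083 |
|---|---|---|---|---|---|---|
| A | 1.22-1.25 | 1.53-1.56 | 3.86-3.95 | 87-89% | 97% | 22-21 |
| B | 1.05-1.08 | 1.31-1.35 | 3.32-3.42 | 73-76% | 91-92% | 29-28 |
| C | 1.00-1.02 | 1.25-1.28 | 3.16-3.23 | 67-70% | 88-89% | 32-31 |

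A more extreme pattern, in which one supplement carries the whole effect, gives λ = 20d², d = 0.86, and 51% for the pair (77% at 0.05). I keep it outside the main range, since it is furthest from a sizing built on co-supplementation.

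**Step 3: how often the level matters.** The chance that the pair's p-value falls between 0.0083 and 0.05 is the power at 0.05 minus the power at 0.0083: about 9-10% under A, 16-18% under B and 19-20% under C.

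**Step 4: baseline adjustment.** At n = 20 and level 0.0083, 90% power needs d = 1.269. If 1.25 is the SD of the end value (an assumption) and the baseline correlation is ρ, ANCOVA raises the effective difference to d/√(1 − ρ²). The ρ that restores 90% is √(1 − (d/1.269)²): about 0.17-0.27 under A, 0.52-0.56 under B and 0.59-0.62 under C. The article gives no ρ.

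**The case against.** The sample-size section names an analysis-of-variance method. The natural reading is that control versus co-supplementation supplies the gap between the extreme means, and that α 0.05 and 90% belong to the four-group F test. The analysis section plans the matching four-group ANCOVA. On that reading the sized test has its stated power and the pair falls short by only 1-3 points, which a weak baseline correlation would make up. An overall test followed by Bonferroni pairs is conventional. It raises no material error-rate problem: under the global null, either the F test or some Bonferroni pair rejects in 5.4% of simulated trials. All of this stands.

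It rules out two stronger conclusions that a reader might infer. The first is that the trial does not deliver its stated power. The document does not support this, because the 90% may refer to the four-group test, the target difference is unknown, and the effect of baseline adjustment cannot be computed. The second is that a p-value between 0.0083 and 0.05 is positive under one section and negative under the other. A sample-size calculation is not a decision rule; only the Statistical analysis section governs inference, and it adjusts the pairs.

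What the objection does not remove is that the four-group test cannot attribute a difference to co-supplementation, and no power is given for the test that can. Both the sizing α and the pairwise rule are stated in the article, so this is not a matter of detail left to a fuller plan.

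**Conclusion.** The point holds in a limited form. The 90% is compatible with the four-group test but is not shown for the Bonferroni-adjusted pair on which the co-supplementation question rests. Without baseline adjustment, the pair is below 90% in every case tried at 20 per group: by 1-3 points under the reading closest to the named method, and by about 14-23 points under readings B and C. These sizes depend on back-solved differences, on all six pairs being tested, and on 20 completers per group. If all 25 per group completed, the pair would have about 94-96% under A and 80-87% under B and C. Baseline adjustment could close some or all of the gap. Worth correcting, with medium confidence, because the remedy is cheap and needs no extra patients.

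**What to change.** In the Statistical analysis section, name co-supplementation versus placebo for TNF-α, estimated from the baseline-adjusted ANCOVA, as the first pairwise contrast, tested at two-sided 0.05. Test the other five TNF-α pairs only if it is significant, with Bonferroni at 0.05/5 = 0.01 each. Family-wise error across these pairs stays at 0.05: if the first null hypothesis is true, any pairwise rejection requires a false rejection at 0.05; if it is false, the other five share 0.05. The first contrast then has about 88-97% power under the three readings before baseline adjustment, although reading C still leaves it slightly short of 90%.

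The cost is one or two sentences before unblinding, and the other five pairs become conditional on the first.

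If Bonferroni over all pairs is kept, say in the Sample size section that the 90% refers to the four-group test, and give the TNF-α difference used, the number of pairs, and the lower power of the control versus co-supplementation pair at the Bonferroni level. This costs a less favourable power figure.

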### Randomization and blinding

The randomization assignment will be performed using computer-generated random numbers. The 100 participants who meet the criteria will be randomly allocated into four groups: 1) a 50,000 IU vitamin D soft gel (weekly) plus 2 omega-3 fatty acid capsules (daily), each capsule containing 330 mg omega-3 fatty acid; 2) a 50,000 IU vitamin D soft gel (weekly) plus 2 omega-3 fatty acid placebo (daily); 3) a vitamin D placebo (weekly) plus 2 omega-3 fatty acid capsules (each capsule containing 330 mg omega-3 fatty acid); and 4) a vitamin D placebo (weekly) plus 2 omega-3 fatty acid placebo (daily). Each omega-3 fatty acid capsule (MorDHA VISION, Minami Nutrition, Belgium) contains 54 mg EPA, 250 mg DHA, and 26 mg of other omega-3 fatty acids. The 50,000 IU vitamin D soft gels are supplied by Zahravi, Iran. The vitamin D and omega-3 fatty acid placebo contain oral paraffin and corn oil, respectively, are supplied by Zahravi, Iran, and are carefully matched in appearance with vitamin D and omega-3 fatty acid soft gels. Patients will receive verbal and written counseling on how to consume the capsules. Compliance will be evaluated by capsule count every 2 weeks. The supplementation will begin before the first session of chemotherapy.

For blinding, a person not involved in the study protocol will create the randomization list, assigning participants to the vitamin D, omega-3, co-supplementation, or placebo group. Vitamin D, omega-3, and placebo tablets will be placed into unlabeled identical containers. The study leader will label these containers with participant numbers using the randomization list. All investigators and participants will be blinded to the random assignments.

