### Participants

Participants will comprise 100 patients with stage II or III CRC. The inclusion criteria will consist of: patients with stage II or III CRC if they have to begin chemotherapy; aged > 18 years; BMI range of 18.5–30 kg/m^2^; serum 25(OH)D < 30 ng/ml; not having autoimmune disease, diabetes, hypertension, or renal, hepatic, parathyroid, and gastrointestinal disorders; not taking vitamin D and/or omeaga-3 supplements and other vitamin/mineral supplements or parenteral nutrition; not taking laxative and/or anti-inflammatory medications; not allergic to fish and fish products; and without history of having other cancers. Exclusion criteria will consist of: affected by any acute disease during the study; changes to the chemotherapy plan; refusal to continue with chemotherapy; unwilling to continue the study; also, we will exclude patients who were less than 90% compliant with treatment.

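### The study leader labels containers from a list of named treatment groups, so the statement that all investigators are blinded cannot stand as written

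*Protocol article*

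**What the plan says.** The procedure is in the protocol article, section Randomization and blinding. It has four steps and a closing claim.

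- List creation: "a person not involved in the study protocol will create the randomization list".
- Content of the list: it is described as "assigning participants to the vitamin D, omega-3, co-supplementation, or placebo group".
- Packing: "Vitamin D, omega-3, and placebo tablets will be placed into unlabeled identical containers".
- Labelling: "The study leader will label these containers with participant numbers using the randomization list".
- Claim: "All investigators and participants will be blinded to the random assignments".

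The section Participants provides for removals once the study is under way. The grounds are "affected by any acute disease during the study; changes to the chemotherapy plan; refusal to continue with chemotherapy; unwilling to continue the study", and in addition "we will exclude patients who were less than 90% compliant with treatment". The article names nobody as responsible for enrolment or for these removals, and it does not define the term study leader.

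**The concern.** The plan brings in an outside person to make the list, which protects allocation only while the list stays away from the people running the trial. It then gives the use of that list to the person leading the study, and in the next sentence says that no investigator knows the assignments.

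Two things are at stake. The first is the double-blind label, which appears in the title, the abstract and the Design section. A reader judging concealment and blinding will rely on this paragraph. The second is the integrity of decisions that could be influenced by knowing the allocation: whom to enrol next, whom to remove after randomisation, and which analysis choices to make. Whether the second is actually affected depends on what the study leader does, and the article does not say.

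**Working it through.** No arithmetic decides this point; it is a matter of reading adjacent statements against each other.

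1. **What labelling requires.** The containers are identical and unlabelled. There are four groups, formed from active or placebo vitamin D and active or placebo omega-3. To put the correct participant number on a container, the labeller must link three things: the number, its group and the container's content.

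2. **What the list shows.** It is described by named group. No code such as A, B, C or D is mentioned. Someone using it to number containers would therefore see which group each number belongs to.

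3. **Whether anything intervenes.** The section does not say that containers are coded by a third party before labelling, that the list is given to the study leader in masked form, or that the study leader is separate from the investigators.

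4. **Against the claim.** The blinding sentence covers all investigators without exception. On the ordinary meaning of the words, a study leader is an investigator. Steps 1 to 3 give that person sight of allocations, so the labelling sentence and the blinding sentence cannot both be true as written.

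5. **Where knowledge of allocation could act.**
   - *Enrolment:* only if the study leader screens or enrols. No role is stated.
   - *Removals after randomisation:* the acute-disease ground is not defined and leaves room for discretion. A change of chemotherapy plan may do so, but the article does not say who makes that decision. Refusing chemotherapy and being unwilling to continue are the patient's decisions. The 90% compliance rule is a numerical cut-off applied to capsule counts every 2 weeks (Randomization and blinding), so it leaves little to judgement.
   - *Outcome measurement:* under Measurements, the biomarkers are ELISA assays, and body measures come from a scale, a height measurement and bioimpedance. These leave little room for an assessor's expectation. Diet, physical activity and sun exposure come from records and questionnaires and are more exposed.
   - *Analysis:* the section Statistical analysis gives the ANCOVA covariates by example, so some choice may remain for whoever carries out the analysis.

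6. **Timing.** Under Trial status, recruitment began on 4/30/2018 and was due to be completed on 5/15/2019. Protocol version 4 is dated 5/4/2019, which is 11 days before that end date. Most containers may already have been labelled.

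**The case against.** The strongest reply is that the article is a condensed account. It does not say who fills the containers, whether the labeller knows their content, or in what form the list reaches the study leader. Masked codes on both list and containers would remove the conflict, and a fuller protocol may describe them. Nor does the article give the study leader any part in enrolment, exclusion or assessment, so concealment could be intact in practice.

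Much of this stands, and it limits what may be claimed. A reader might infer that the study leader knows the content of every container and can foresee every coming assignment, so that concealment has failed. The text does not go that far: that is the natural consequence of a named-group list, but it is not stated, and foresight harms concealment only if the same person enrols. A reader might also infer that the compliance exclusion invites biased judgement; a fixed cut-off on a capsule count does not support that. Nor can a size of bias be derived. Two patients would be 2/25 = 8% of a recruited group, or 2/20 = 10% of the number required per group, but the two is arbitrary, and a share of the data is not an effect on an estimate.

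The reply does not remove the contradiction. The article does not merely omit the procedure. It states it, names who performs it, and follows it with a claim that the procedure defeats.

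**Conclusion.** The point holds as an internal contradiction. As written, the study leader has access to assignments, and the double-blind claim is not true for that person. This is an incorrect statement about a core safeguard, not a detail left to another document.

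Its extent is up to all 100 allocations, open to one person. Its effect on the results is conditional and cannot be quantified from the article. If the study leader enrols patients or decides discretionary removals, concealment and those removals are open to bias. If not, the damage is confined to an inaccurate blinding statement. Bias in the assays and body measurements is likely to be small either way.

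The conclusion rests on two assumptions: that the study leader counts as an investigator, and that the list is used in the named-group form in which it is described. If either is wrong, the article needs to say so.

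**What to change.** **Containers not yet labelled.** The independent person who creates the list should also number the containers and hold the list until database lock. The study leader then receives only numbered containers. This moves one packing step to someone already in the plan and changes one sentence.

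**Containers already labelled.** On the dates given this may be most or all of them, and renumbering cannot restore concealment that has been lost. Keep the study leader out of any remaining eligibility, exclusion, measurement and pre-lock analysis decisions.

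**In either case.** Replace the sentence about all investigators with an accurate account of who had access to the list, in what form, and what part they took in enrolment, exclusions, measurement and analysis. If masked codes were used, say so. If the study leader had access and also took part in those decisions, report it as a limitation and qualify the double-blind description. The text change costs almost nothing. Keeping the study leader apart may mean passing some decisions to a colleague without access to the list.

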### Measurements

A questionnaire about patients’ medications, diseases, cancer history, and probable supplement use will be recorded at the beginning of the intervention. Dietary intake will be evaluated by 3-day, 24-h record questionnaires (two week days and one weekend day) at baseline and the end of the intervention, and total energy, macronutrient, and some micronutrient (vitamins A, D, E; calcium and selenium) intake will be estimated using nutritionist IV software. To evaluate physical activity levels the short form of the international physical activity questionnaire (IPAQ) [27] will be used at baseline and the end of the intervention. Sun exposure will be assessed with the questionnaire [28] at baseline and the end of the study. A sunshine exposure score is obtained based on (a) how often and what time of day the subjects are outside, (b) which parts of the body are exposed as a percentage of total body surface area, and (c) do the subjects use sun screen or not. Anthropometric indices will be measured after overnight fasting, with minimal clothing and without shoes, before and after the intervention. Body weight will be measured to an accuracy of 0.1 kg using a Beurer scale (Beurer, Germany). Height will be assessed to the nearest 0.5 cm in the standing position without shoes. BMI will be computed as body weight (kg) divided by height squared (cm^2^). A bioelectric impedance analyzer (Quad scan 4000; Body stat) will be used to measure total body fat and fat free mass percentage. The difference in CRP/albumin levels, as an indicator of nutritional status, between groups will also be compared with score values proposed by Correa et al.: no risk ≤ 0.4; low risk = 0.4–1.2; medium risk = 1.2–2; high risk ≥ 2.0 [29]. This indicator will be assessed at baseline and end of the intervention.

Before and after the intervention, blood samples will be collected after 12-h overnight fasting. The serum of patients will be kept at − 80 °C until biochemical analyses. Serum 25(OH)D will be measured by enzyme-linked immunosorbent assay (ELISA) and Euro Immun kit (Euro Immun, Germany). Serum TNF-α, IL-1β, IL-6, and IL-8 levels will be assessed by ELISA and Bender Med kit (Bender Med, Germany). Serum CRP and albumin will be determined by ELISA and Binding kit (Binding, UK). Tumor marker CEA will be evaluated by ELISA and CanAg kit (CanAg, Italy).

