### Objectives and hypotheses of the study

The primary objective of the present study is to assess the impact of 8-week vitamin D_3_ and omega-3 fatty acids co-supplementation on serum 25(OH)D, inflammatory biomarkers, CRP/albumin, tumor marker CEA, body mass index (BMI), and body composition in patients with stage ӀӀ or ӀӀӀ CRC undergoing chemotherapy. As a second objective, the study will also evaluate the relationship between alterations in 25(OH)D levels and other variables. It is also expected that there will be improvement in evaluated variables.

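### Fat-free mass percentage and CRP/albumin cannot by themselves show a nutritional gain; kilogram masses, albumin and CRP should be analysed beside them

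*Protocol article*

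**What the plan says.** The section on objectives puts these outcomes together in the primary objective: "inflammatory biomarkers, CRP/albumin, tumor marker CEA, body mass index (BMI), and body composition in patients with stage" II or III disease on chemotherapy. It expects improvement but does not say which direction counts as improvement for BMI or body composition.

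Measurements then fixes how they are obtained:

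- Body composition: a bioimpedance analyser "will be used to measure total body fat and fat free mass percentage".
- Weight: "Body weight will be measured to an accuracy of 0.1 kg using a Beurer scale", before and after the intervention.
- Nutritional index: "The difference in CRP/albumin levels, as an indicator of nutritional status, between groups" is compared, and four risk classes are given: "no risk ≤ 0.4; low risk = 0.4–1.2; medium risk = 1.2–2; high risk ≥ 2.0". CRP and albumin are each assayed.
- BMI: "BMI will be computed as body weight (kg) divided by height squared (cm^2", whereas Participants states the eligibility limits as "BMI range of 18.5–30 kg/m^2".

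The Discussion sets out the reasoning behind the nutritional question: the supplements are supposed to lower inflammation, and better nutrition is supposed to follow from that.

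**The concern.** Nutritional status is one of the three outcome domains in the trial's title, and the patients are starting chemotherapy. The Background lists less cancer-related cachexia among the suggested omega-3 mechanisms, so loss of lean tissue matters here.

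A percentage of body weight has a moving denominator. When weight falls, fat-free mass percentage can rise while the patient loses lean tissue.

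CRP/albumin has an inflammation marker as its numerator. The hypothesis has two steps: inflammation falls, then nutrition improves. If the first step alone occurs, the ratio already moves in the favourable direction. A group difference in the ratio is therefore not evidence for the second step. If these two measures are read as nutritional results without their components, a gain could be reported while lean mass or albumin is falling or unchanged.

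**Working it through.** The protocol gives no figure to reproduce on this point. The body weights, fat fractions, height, CRP and albumin values below are assumptions for illustration.

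**Fat-free mass percentage.** Let W be baseline weight, f the baseline fat fraction, L the weight lost and s the share of the loss that is fat.

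- Fat-free mass after the loss, in kg: W(1 − f) − L(1 − s).
- Fat-free mass percentage after the loss: [W(1 − f) − L(1 − s)] / (W − L).
- This exceeds the baseline value 1 − f exactly when 1 − s < 1 − f, that is, when s > f.

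With L = 5 kg:

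| Baseline | Fat share of loss | Fat-free mass, kg | Fat-free mass, % |
|---|---|---|---|
| 70 kg, 30% fat | 60% | 49.0 → 47.0 | 70.0 → 72.3 |
| 70 kg, 30% fat | 30% | 49.0 → 45.5 | 70.0 → 70.0 |
| 70 kg, 30% fat | 20% | 49.0 → 45.0 | 70.0 → 69.2 |
| 70 kg, 25% fat | 30% | 52.5 → 49.0 | 75.0 → 75.4 |
| 80 kg, 35% fat | 30% | 52.0 → 48.5 | 65.0 → 64.7 |

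First row: 49.0 − 5 × 0.4 = 47.0 kg, and 47.0/65 = 72.3%. Lean mass falls in every row. The percentage rises in two, stays level in one and falls in two, according to whether s is above, equal to or below f.

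**CRP/albumin.** Take CRP in mg/L over albumin in g/dL (assumed, because the cut-offs are printed without units).

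- Baseline: 8/4.0 = 2.0, high risk as printed, although 2 also closes the medium band.
- CRP halved, albumin unchanged: 4/4.0 = 1.0, low risk.
- CRP halved, albumin down 10%: 4/3.6 = 1.11, still low risk.
- CRP unchanged, albumin up 10%: 8/4.4 = 1.82, a fall of 1 − 1/1.1 = 9%.

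The class labels depend on the assumed units and values, but the proportional changes do not. Halving CRP halves the ratio. Halving CRP with albumin down 10% multiplies it by 0.5/0.9 = 0.56. So the ratio can improve substantially while albumin worsens.

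**BMI.** For 70 kg at 170 cm, 70/1.70² = 24.2 kg/m², while the printed formula gives 70/170² = 0.00242. The factor is a constant 10,000, so the direction of change, group contrasts and p-values are unaffected. For the 70 kg patients in the table, BMI at 170 cm falls from 24.2 to 65/1.70² = 22.5.

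**The case against.** Several points on the other side stand.

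- The percentage problem is conditional. A reader might infer that fat-free mass percentage always hides wasting. It does so only when the fat share of the loss exceeds the baseline fat fraction; below that, it falls as it should.
- BMI is a named outcome and weight is measured before and after, so the weight loss itself would be seen. A reader might infer that the whole outcome set would conceal deterioration. It would not. But BMI does not separate lean from fat, and no favourable direction is fixed for it in a population admitted up to 30 kg/m².
- A reader might infer that fat and fat-free mass are one variable counted twice. That needs body fat to be a percentage too, and the sentence leaves open whether the word percentage covers both.
- A reader might infer that CRP is certainly counted twice, as inflammation and as nutrition. The protocol names CRP only as an assay and within the ratio, and does not list which inflammatory biomarkers are outcomes.
- CRP/albumin is a cited index, called one indicator and not the only one. Its validity rests on a source not available here. The point concerns only what the ratio can distinguish, which follows from its form.
- Nothing says that albumin will go unreported, and an article may leave derived variables to a fuller document. But the scale of fat-free mass and the choice of the ratio as nutritional indicator are fixed in this text, and the primary objective names the ratio and not albumin.

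**Conclusion.** The point holds for both measures, within limits. As fixed, fat-free mass percentage can rise while lean mass falls: in the 60% case it rises 72.3 − 70.0 = 2.3 percentage points against a loss of 2.0 kg, or 2.0/49.0 = 4% of lean mass. CRP/albumin cannot separate a nutritional effect from the anti-inflammatory effect that the Discussion supposes comes first. The first statement depends on the fat share of the loss, for which the protocol gives no figure. The second holds whatever the values. Neither affects the sample size, and neither shows that the trial will reach a wrong result. The protocol also never declares a rise in fat-free mass percentage to be a benefit.

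The BMI formula contradicts the eligibility units, but it is a separate wording slip. A reader might infer from the factor of 10,000 that BMI results would be distorted. A constant factor cannot do that, nor can it make weight loss look like gain.

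**What to change.** 1. Derive and analyse fat-free mass and fat mass in kilograms (weight × fraction, or weight minus the other component if the analyser gives one in kilograms). Keep percentages as supplementary, and state the unit of body fat. The planned baseline-adjusted ANCOVA can be used unchanged.
2. Analyse albumin and CRP as outcomes of their own beside the ratio. Interpret a change in the ratio as nutritional only in light of the albumin result.
3. Separately, correct the BMI formula to height in metres squared, to agree with the eligibility range.

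The cost is a few more derived variables and outcomes to report. Weight, impedance, CRP and albumin are already collected, so no new measurement, visit or patient is needed.
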